### Data collection methods

The main outcomes were collected by means of a Data Collection Logbook specially designed for this study. This logbook included the outcome measures previously described. One member of the investigation team was responsible for the collection and processing of data related to main outcome variables. To promote participant retention, patients performed 2 weekly supervised sessions; any patient not attending these scheduled sessions was contacted by telephone.

### Data management

Two researchers were in charge of the database. On the basis of the information collected on the Data Collection sheets, one of them entered data into the database, and the second researcher checked data accuracy. No personally identifying information was registered and a code number was assigned to each participant. A list with code numbers was used to randomize patients to control or intervention groups by an external researcher not involved with the trial procedures.

### Statistical analysis

Descriptive statistics summarizes the demographic and clinical outcomes of the participants. Assumption of normality is analysed using normality charts and the Kolmogorov-Smirnov test corrected with the Lilliefors test. The bivariate analysis is performed using the chi-square, Fisher exact, Student t or Mann-Whitney U tests, depending on the variables analysed.

Treatment effect is analysed in two ways: changes in PImax and PEmax pre- and post-intervention (ΔPImax and ΔPEmax, respectively) and by calculating the percentage change using the formula [((post value − pre-value) /pre-value) × 100]. Changes during follow-up are assessed by analysis of variance using mixed repeated measures and a one-factor design for the analysis of values over time.

All statistical tests are two-tailed and statistical significance has been set at 0.05. IBM SPSS 22.0 software is used for statistical analysis. The final report will follow CONSORT 2010 guidelines.

When estimating the study’s sample size, the possibility of loss to follow-up was considered and factored into the calculation. Moreover, other missing data was accounted for by handling drop-outs as non-finishing intervention, in accordance with the intention-to-treat principle.

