### Participant timeline

The principal investigator screened the eligibility of potential participants during hospital admission as of April 2017. These patients received detailed information about the study procedures and were invited to participate. Demographic and clinical characteristics of the participants were collected at baseline (T0). Primary and secondary outcomes were assessed at baseline (T0), after 8 week-exercise intervention (T1) and 6-month follow-up (T2), as shown in Fig. 1.

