### Sample size

Accepting an alpha risk of 0.05 and a beta risk of 0.2 in a two-sided test, 25 patients are required in each group to detect a difference of 27 (SD 31) cmH_2_O in PImax, anticipating potential losses of 15% (final size 50 patients). These assumptions have been based on data of de Menezes et al. [14]. The sample size was calculated using the GRANMO Sample Size and Power Calculation software of the Hospital del Mar Research Institute (IMIM).

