### Allocation

This trial was designed as a parallel-group double-blind randomized controlled trial with allocation ratio 1:1 in a superiority framework of the intervention and intention-to-treat analyses. Allocation to study groups was performed independently by a member of the medical staff blinded to patient identity using a randomization programme designed by the IT Department. Patients and researchers in charge of assessments were blinded to study group assignments. Patients were randomly allocated to either an intervention (IEMT) group or a control (sham) group. Allocation concealment was ensured as the person in charge of randomization did not release the randomization codes until participants completed all measurements. Training began at hospital discharge. Outcome measures were collected by a trained research worker at baseline (week 0), at the end of training (week 8) and 6 months after cessation of training. Data collection and analysis are carried out by a research worker blinded for the allocation group.

Study sites and phases are summarized in the flow chart diagram (Fig. 2).

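### The effect on PImax and PEmax is set as both raw change and percentage change, with neither named primary and no adjustment for the baseline that is measured in everyone

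*Protocol article*

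**What the plan says.** The Statistical analysis section sets the measure of effect directly: "Treatment effect is analysed in two ways: changes in PImax and PEmax pre- and post-intervention", and then "by calculating the percentage change using the formula [((post value − pre-value) /pre-value) × 100". It ranks neither above the other. The between-group tests it lists are Student t, Mann-Whitney, chi-square and Fisher exact, none of which takes a covariate. The one model named is a mixed repeated-measures analysis of variance for changes during follow-up, and no baseline covariate is given for it.

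Baseline values will be available: "Primary and secondary outcomes were assessed at baseline (T0), after 8 week-exercise intervention (T1) and 6-month follow-up (T2").

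The Sample size section works in absolute units: "25 patients are required in each group to detect a difference of 27 (SD 31") cmH2O in PImax. It does not say whether 31 is the SD of the change or of a single measurement, and it assumes nothing about percentage change.

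The unit is also unsettled. Study outcomes expresses PImax and PEmax in cmH2O. The respiratory muscle pressures item under Data collection, management and analysis says that the analysed value is a percentage of reference values.

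**The concern.** Two measures of equal standing can disagree, for each of two pressures. With no primary measure named, the headline result can be chosen after the data are seen.

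Both measures also make poor use of the baseline. Raw change subtracts the whole baseline value whatever its correlation with the week-8 value, which usually costs precision compared with fitting baseline as a covariate. Percentage change divides by a noisy baseline, so the weakest patients can dominate and the distribution becomes skewed. With about 20 evaluable patients per arm, there is little power to spare.

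This is not a detail left to an unseen analysis plan, because the article states the two measures as its choice.

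**Working it through.** **Inputs from the protocol article**
- "Accepting an alpha risk of 0.05 and a beta risk of 0.2 in a two-sided test"; difference 27, SD 31, 25 per group; "anticipating potential losses of 15% (final size 50 patients") (Sample size).
- 1:1 allocation (Allocation).
- 48 enrolled (Trial status).

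**Inputs assumed, because the documents do not give them:** baseline mean, baseline SD, and the correlation ρ between baseline and week 8.

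**1. The plan's own figure.** n per arm = 2(1.960 + 0.842)² × 31² / 27² = 20.7, so 21 evaluable. 21 / 0.85 = 24.7, so 25 per arm and 50 in total. The stated size reproduces. Power at 21 per arm is 0.806 by the normal approximation.

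**2. Evaluable patients now.** 48 × 0.85 = 40.8, about 20 per arm. The standardised difference is 27 / (31 × √(2/20)) = 2.75. Power is 0.79 by the normal approximation and 76.5% by the exact t test.

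**3. Raw change against baseline adjustment, if 31 is the SD of change and visit SDs are equal.** Adjusted SD = 31 × √((1 + ρ)/2). At 20 per arm (two-sample t power):

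| ρ | Adjusted SD | Power, adjusted | Power, raw change |
|---|---|---|---|
| 0.5 | 26.8 | 87% | 77% |
| 0.7 | 28.6 | 83% | 77% |
| 0.8 | 29.4 | 81% | 77% |

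**4. The same comparison if 31 is a single-visit SD.** Change SD = 31 × √(2(1 − ρ)); adjusted SD = 31 × √(1 − ρ²). At 21 per arm, normal approximation, adjusted against raw change: 0.84 v 0.67 at ρ = 0.3, 0.90 v 0.81 at 0.5, 0.98 v 0.95 at 0.7.

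**5. Percentage change.** There is no closed form, so it was simulated with an additive effect of 27, 3,000 to 4,000 trials per setting, and low baselines limited at 10 or 15 cmH2O.

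| Baseline mean | SD, baseline / week 8 | ρ | n per arm | Adjusted | Raw change | % change, t test | % change, Mann-Whitney |
|---|---|---|---|---|---|---|---|
| 60–80 | 31 / 31 | 0.5 | 20 | 86–87% | 77–79% | 49–53% | 64–66% |
| 80 | 31 / 31 | 0.7 | 20 | 96% | 93% | 70–71% | 84% |
| 80 | 20 / 31 | 0.5 | 21 | 88% | 88% | 82% | not run |
| 80 | 20 / 31 | 0.7 | 21 | 97% | 97% | 96% | not run |

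In the last row the unrounded values are 97.2% for raw change and 95.6% for percentage change, a loss of 1.6 points. In the last two rows adjustment gains nothing over raw change, because the week-8 SD exceeds the baseline SD and the regression slope, ρ × 31/20, is 0.78 and 1.09, near the value of 1 that raw change imposes.

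The first row is sensitive to the handling of very low baselines. A second simulation with 21 per arm gave 58–59% for percentage change by t test, against 80% for raw change.

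**6. The repeated-measures analysis.** With two visits its group-by-time test is the t test on change. It is not an adjustment for baseline.

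**The case against.** The strongest reply is that raw change is a legitimate analysis. It is unbiased under randomisation, and if 31 is the SD of change it delivers the planned power of 0.81 at 21 per arm. Adjustment then improves an acceptable method. That stands. A reader might infer that chance baseline imbalance biases the change score. It does not: imbalance affects the one realised estimate and its precision, not the expectation over randomisations.

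A reader might also infer that percentage change necessarily wastes a large share of the power. The documents cannot show that, because they give no baseline mean, SD or correlation, and the loss runs from about 2 to 29 points across plausible values. Mann-Whitney recovers part of it.

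Two further inferences go too far. Closing at 48 patients is not a serious loss: on the plan's normal approximation power moves from 0.81 to 0.79, and the 77% above comes mainly from using the exact t test. Nor does the article say that a normality test decides how change scores are compared. It lists a normality check and says that tests depend on the variables analysed. Data-driven switching is a plausible reading, but it is not stated.

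None of this answers the remaining point: two measures, no primary, and a measured baseline left unused.

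**Conclusion.** The point holds as a matter of specification and efficiency, not of bias. The article fixes two measures of effect without ranking them and adjusts neither for baseline.

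- **Raw change against adjustment:** about 4 to 10 power points at 20 per arm for ρ from 0.8 down to 0.5, if 31 is the SD of change and visit SDs are equal. The gap is wider if 31 is a single-visit SD and ρ is low, and nil if week-8 values are sufficiently more variable than baseline.
- **Percentage change against raw change, by t test:** roughly 20 to 30 points with SD 31 at both visits and ρ = 0.5, about 22 points at ρ = 0.7 (mean 80), and about 2 points with baseline SD 20, mean 80 and ρ = 0.7.

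The direction is secure. The size for percentage change is conditional on assumed values and should be quoted only as a range. Apart from power, percentage change lacks any support in a sample size set in cmH2O.

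**What to change.** Name one primary estimate: the between-arm difference in week-8 (T1) PImax, and likewise PEmax, in cmH2O, from a linear model with arm and baseline value, with a 95% confidence interval. State that no normality test changes this model. Keep raw change as supportive and percentage change as descriptive only.

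Reconcile the unit first: Study outcomes gives cmH2O, while the respiratory muscle pressures item has the analysed value as a percentage of reference values.

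The cost is small but not zero. No new data are needed, and the named software fits the model. Follow-up ended in September 2020, so the change needs a dated amendment before unblinding. The Blinding section still places completion of the analysis in the future. If allocation is already known to the analysts, report the adjusted estimate as post hoc alongside the analyses in the article.

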### Study outcomes

Two primary *outcomes* are contemplated: strength of the inspiratory and expiratory muscles after an 8-week IEMT protocol, estimated with maximal inspiratory and expiratory pressures (PImax and PEmax, respectively) expressed in cmH_2_O, and dysphagia severity assessed by VFSS. Secondary outcomes are voluntary peak cough flow (measured using a PEFR meter) and tongue strength (measured with the IOPI® system). All data was collected at baseline, end-treatment and 6-month follow-up.

Respiratory complications were also registered during the follow-up by asking the participants and were checked in the personal health history if whether they had been admitted to a hospital (Public Health System, on-line access) for respiratory causes (e.g. pneumonia or lung infections).

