### Data collection, management and analysis

*Instruments for swallowing and respiratory function study:*
*Swallowing function parameters:*
1.1.*Videofluoroscopy* was selected for examination of swallowing function. The lateral profile sequence of fluoroscopy was captured by continuous recording with digital storage of images at a rate of 25 frames per second. Visipaque®, a water-soluble contrast, and Thickener Resource®, a ThickenUp, were used to obtain 3 distinct viscosities (liquid, nectar, pudding). Water-soluble contrast is available in bottles of 50 mL (16 mg iodine) or 320 mg/mL. Liquid viscosity was obtained by mixing 1:1 mineral water and water-soluble contrast at room temperature (100 mL/16mg iodine); thickener was added to the liquid solution in a mixing pan to obtain nectar and pudding viscosity (3.5 g and 8 g of thickener, respectively). Solutions were prepared 10 min before measurement. For each viscosity and soft solid, boluses in increasing volumes of 5, 10 and 20 mL were offered to patients with a syringe. The worst punctuation obtained regardless of the altered viscosity was determined on the Penetration-Aspiration Scale [20] and the amount of residue generated on the Bolus Residue Scale (BRS) [21]. Both values were recorded for statistical analysis.1.2.*Fiberoptic endoscopic evaluation of swallowing, FEES*: At 6 months after the stroke event, swallowing function was assessed using a standardized FEES examination. During FEES, patients are seated in an upright position and a flexible endoscope (Xion system©) introduced into the inferior turbinate in the inferior meatus; it will then be passed through the oropharynx to a point posterior to the epiglottis where the general appearance of the laryngeal structures can be clearly visualized. The patient is asked to phonate, to enable assessment of the adequacy of vocal fold adduction. At this point, three consistencies were administered for consecutive trials of 5/10/20 cc of thick liquid (applesauce dyed with green food colouring), 5/10/20 cc of thin liquid (water dyed with 5% methylene blue) and 5 ml of pudding bolus. The bolus consistencies were administered in the same sequence for all patients. FEES images were obtained and recorded on a DVD [22]. A Penetration-Aspiration Scale (PAS) [23, 24] was used to detect entry or residue. The worst punctuation obtained on each scale, regardless of the altered viscosity, was recorded for statistical analysis.Both techniques were performed by a 10-year experienced senior medical staff, blinded for the training programme allocation.

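### Dysphagia severity is a primary outcome, but the treatment effect is defined only for PImax and PEmax; a baseline-adjusted ordinal comparison at T1 should be named

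*Protocol article*

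**What the plan says.** Study outcomes in the protocol article opens with "Two primary *outcomes* are contemplated: strength of the inspiratory and expiratory muscles after an 8-week IEMT protocol" and gives dysphagia severity on VFSS as the second of the two. Data are collected at baseline (T0), end of treatment (T1) and 6-month follow-up (T2).

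The videofluoroscopy paragraph under Data collection, management and analysis explains the scoring: "The worst punctuation obtained regardless of the altered viscosity was determined on the Penetration-Aspiration Scale". A Bolus Residue Scale (BRS) value is taken as well, and both are recorded for analysis. The article does not say which of the two represents dysphagia severity.

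Statistical analysis then states: "Treatment effect is analysed in two ways: changes in PImax and PEmax pre- and post-intervention", followed by a percentage-change formula. Neither swallowing score is mentioned anywhere in that section. Two general provisions remain:

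- a list of bivariate tests (chi-square, Fisher exact, Student t, Mann-Whitney U), chosen according to the type of variable;
- the longitudinal sentence, "Changes during follow-up are assessed by analysis of variance using mixed repeated measures and a one-factor design for the analysis of values over time".

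**The concern.** The article does fix a treatment-effect analysis, and it restricts that analysis to one of its two primary outcomes. For the other, the reader must guess the score, the time point and the test.

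The listed tools fit the worst PAS score unevenly. An unadjusted Mann-Whitney test respects its ordinal nature but, applied to T1 scores, leaves the collected baseline unused. A repeated-measures ANOVA brings T0 in but treats category numbers as equally spaced. A one-factor analysis over time contains no arm comparison. Both arms receive standard swallowing therapy, and the Introduction cites work in which respiratory function and cough improved early after stroke without a training benefit. Improvement within an arm would therefore not answer the superiority question.

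At stake are a primary claim whose analysis could be chosen after the data are seen, and precision in a trial that closed at 48 patients and was sized on PImax alone.

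**Working it through.** **1. The plan's own sample size, for context.** Inputs from Sample size: two-sided α = 0.05; power 0.80; PImax difference 27 cmH2O with SD 31; losses 15%. Stated result: 25 per arm.

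n per arm = 2(1.960 + 0.842)² × 31² / 27² = 20.7, so 21. Allowing for losses, 21 / 0.85 = 24.7, so 25 per arm and 50 in total. The stated figure is reproduced and is not in dispute. It concerns PImax only; no corresponding calculation is given for swallowing.

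**2. How each listed tool treats the T1 swallowing score.**

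| Tool | Compares arms | Uses T0 | Respects ordinal scale |
|---|---|---|---|
| Mann-Whitney on T1 | yes | no | yes |
| Mixed repeated-measures ANOVA (usual group-by-time form) | yes | yes, much like a change score | no |
| One-factor analysis over time | no | yes | no |
| Baseline-adjusted ordinal or rank analysis (not listed) | yes | yes | yes |

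**3. Approximate efficiency.** Let ρ be the T0–T1 correlation, with equal variances. Relative to a T1-only comparison (variance 1), a change score has variance 2(1 − ρ) and an adjusted comparison 1 − ρ².

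| ρ | Change score | Baseline-adjusted |
|---|---|---|
| 0.3 | 1.40 | 0.91 |
| 0.5 | 1.00 | 0.75 |
| 0.7 | 0.60 | 0.51 |

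**4. Simulated power, baseline unrestricted.** None of these inputs is in the article: 8 ordered categories cut from a latent normal, latent shift 0.8 SD, 21 per arm, 3,000 runs per setting. With two time points the change-score t-test is the group-by-time test.

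| ρ | Mann-Whitney on T1 | Change score | Rank ANCOVA | Gain over Mann-Whitney |
|---|---|---|---|---|
| 0.3 | 65% | 44% | 68% | about 2 points |
| 0.5 | 64% | 53% | 73% | 9 points |
| 0.7 | 63% | 70% | 85% | 22 points |

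Type I error was 4.3% to 5.1% for these three methods. A separate run with 20 per arm (48 / 2 = 24; 24 × 0.85 = 20.4) put the gain at about 5 to 21 points.

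**5. Simulated power, baseline restricted.** Eligibility requires diagnosed dysphagia, which narrows the baseline range. Taking only the upper half of the latent scale at entry (an assumed cut), with 20 per arm and 3,000 runs:

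| ρ (before selection) | Mann-Whitney on T1 | Change score | Rank ANCOVA |
|---|---|---|---|
| 0.3 | 67% | 65% | 68% |
| 0.5 | 74% | 76% | 76% |
| 0.7 | 83% | 90% | 89% |

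The gain over Mann-Whitney is here 1 to 6 points from the rounded figures; a repeat run gave about 0 to 7. A change score does as well at ρ of 0.5 and 0.7.

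**6. Proportional odds.** A small unrestricted run (400 per setting, 21 per arm) gave power of 65% at ρ = 0.3 and 76% at 0.5, with null rejection of 6.5% and 6.75%. The Monte Carlo standard error is √(0.05 × 0.95 / 400) = 1.1 points, so this is compatible with 5% but does not exclude slight excess.

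**The case against.** The strongest reply is that this is an omission in a condensed article, that a full analysis plan may exist, and that a valid between-arm test is already listed. Much of this stands. Mann-Whitney is appropriate for an ordinal score, and randomisation makes the unadjusted comparison unbiased. What separates the methods is efficiency, which may be slight once the entry criterion narrows baseline severity. The omission argument does not dispose of the point, because the article itself says how the treatment effect is analysed and names only the pressures.

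A reader might also infer three stronger faults that the text does not support:

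- That percentage change is applied to PAS. The formula belongs to the sentence on PImax and PEmax.
- That every listed tool ignores baseline. A mixed repeated-measures ANOVA includes T0 and ordinarily has a group-by-time term.
- That the plan will base its swallowing conclusion on within-arm change. The one-factor analysis stands beside the mixed model, and nothing assigns the treatment claim to it.

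It is fair, too, that adding a model after follow-up has ended is more than an edit of wording unless it is fixed before unblinding, and that ranking PAS above BRS is for the sponsor to decide.

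**Conclusion.** The point holds in a limited form. One of two primary outcomes has no stated treatment-effect analysis. The general tools that could be applied either leave its baseline unused or treat an ordinal category as interval data, and the one-factor time analysis cannot support a between-arm claim. This is a matter of specification and efficiency; the listed Mann-Whitney comparison would not be invalid.

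The likely gain from adjustment over Mann-Whitney lies between about 0 to 7 power points (restricted baseline) and about 5 to 21 points (unrestricted), with no material loss and rank-ANCOVA type I error near 5%. These figures rest on an assumed 8-category scale, a 0.8 SD latent shift, 20 per arm and correlations of 0.3 to 0.7. The article supplies none of the effect size, category distribution or correlation, so no single value should be quoted as the trial's loss.

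**What to change.** Add to Statistical analysis: the primary dysphagia analysis is the between-arm comparison of worst VFSS PAS at T1, adjusted for baseline PAS. Name one method and fix it before unblinding:

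- a proportional-odds model, reporting a common odds ratio with 95% CI; or
- rank ANCOVA.

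The choice should not switch on how sparse the observed categories turn out to be. Analyse BRS in the same way, and have the sponsor state which of the two scores is primary. State that the one-factor analysis over time is descriptive.

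T1 also avoids a measurement difficulty: the methods describe an endoscopic (FEES) examination with different bolus materials at 6 months after stroke, so a PAS series extended to that visit could mix instruments.

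No new data are needed, since baseline scores are already collected. The costs are an odds ratio in place of a mean change and reliance on proportional odds in a small sample; rank ANCOVA avoids the latter but gives a less direct effect estimate. Trial status reports that follow-up ended in September 2020, so the change should be dated. If allocation had already been revealed, the adjusted analysis should be labelled as added afterwards.

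### The two primary outcomes cover three or four variables, each tested at 0.05, and the protocol does not say which result would support the hypothesis

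*Protocol article*

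**What the plan says.** Study outcomes, in the protocol article, declares two primary outcomes. The first, strength after the 8-week programme, is already two variables: it is "estimated with maximal inspiratory and expiratory pressures (PImax and PEmax, respectively) expressed in cmH_2_O". The second is added with the words "and dysphagia severity assessed by VFSS"; no scale is named, and no primary time point is given for it, although all data are collected at baseline (T0), end of treatment (T1) and 6-month follow-up (T2).

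The videofluoroscopy paragraph under Data collection, management and analysis takes the worst score on the PAS and the residue on the BRS, and then says: "Both values were recorded for statistical analysis". Neither scale has priority.

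Statistical analysis examines the treatment effect on PImax and PEmax in two ways, as pre-post change and as percentage change, again without priority. It then sets one level for everything: "All statistical tests are two-tailed and statistical significance has been set at 0.05".

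Sample size rests on one variable: "25 patients are required in each group to detect a difference of 27 (SD 31) cmH_2_O in PImax", under the condition "Accepting an alpha risk of 0.05 and a beta risk of 0.2 in a two-sided test". No effect size is given for PEmax, PAS or BRS.

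**The concern.** With several primary variables, a 5% level per test gives a 5% error for the trial's conclusion only if the plan also says how the results combine. Here it does not. Someone reading the final report could not tell whether a significant PEmax alone, or a significant BRS alone, confirms the hypothesis. The choices of scale, metric and (for swallowing) time point also stay open until the data are seen.

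Two things are at stake. One is the false-positive rate of the primary claim. The other is what the 80% power refers to: swallowing is half of the stated aim, but nothing in the sample size speaks to it.

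**Working it through.** **Inputs from the protocol article.** Two-sided alpha 0.05 for every test (Statistical analysis). Difference 27, SD 31 cmH2O, beta 0.2, losses 15%, 25 per group (Sample size). Allocation 1:1 (Allocation).

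**Assumption.** The correlation between the primary test statistics is not given. A common value r from 0 to 0.9 is shown.

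**1. The plan's own figure.** n per arm = 2 × (1.960 + 0.842)² × 31² / 27² = 2 × 7.85 × 1.318 = 20.7, so 21. With losses: 21 / 0.85 = 24.7, so 25 per arm and 50 in total. This reproduces exactly. Power at 21 per arm is 80.6% by the normal approximation and 78.6% by the noncentral t, for PImax alone at 0.05.

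**2. Error if any one variable counts as success and none is truly affected.** For k independent tests it is 1 − 0.95^k:
- k = 2: 1 − 0.9025 = 9.75%
- k = 3: 1 − 0.8574 = 14.3%
- k = 4: 1 − 0.8145 = 18.5%

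For equicorrelated normal statistics it is 1 − ∫ [Φ((c − √r·g)/√(1−r)) − Φ((−c − √r·g)/√(1−r))]^k φ(g) dg, with c = 1.96:

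| k | r = 0 | r = 0.5 | r = 0.7 | r = 0.8 | r = 0.9 |
|---|---|---|---|---|---|
| 2 | 9.8% | 9.1% | 8.4% | 7.8% | 7.0% |
| 3 | 14.3% | 12.5% | 10.9% | 9.8% | 8.4% |
| 4 | 18.5% | 15.6% | 13.0% | 11.4% | 9.4% |

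Here k = 2 is one variable per named outcome, k = 3 is PImax, PEmax and one VFSS scale, and k = 4 counts both scales. A more structured assumption for k = 4 (correlation 0.5-0.8 within the PImax-PEmax and PAS-BRS pairs, 0-0.3 between pairs) gives 14.5-17.3%.

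**3. Two metrics for one strength variable.** Taking the better of absolute and percentage change moves 5% to between 5.5% and 7.1% in simulations at 21 per arm. The result depends on the baseline mean and SD, which the article does not give and which were assumed. It is a minor addition.

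**4. If all variables must succeed.** The error is at most 5%. Joint power cannot exceed the power for PImax. As an illustration only, if one further variable also had 80% power and were independent, joint power would be 0.80 × 0.80 = 64%; with two further such variables, 0.80³ = 51%.

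**5. What an alpha split would cost PImax** (noncentral t, 21 per arm): 78.6% at 0.05; 68.9% at 0.05/2; 62.8% at 0.05/3; 58.5% at 0.05/4.

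**The case against.** A reader might infer that the protocol lets the trial claim efficacy on whichever variable reaches significance, and so carries a 13-19% false-positive risk. The text does not support that as a flat statement:

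- No any-one-suffices rule is written. The aims in the Abstract and the Introduction join strength and swallowing with an *and*, which may mean that both are required. The error would then not be inflated.
- Four primary variables is an inference. Two outcomes are named, and recording both PAS and BRS for analysis does not make both primary.
- The range requires no true effect on any variable, while the Introduction and Discussion report earlier gains in strength from this training. If strength does respond, only the swallowing scales can give a false positive: 5% for one scale and 9.75% for two independent ones.
- At correlations above 0.7 the four-variable figure falls below 13%.

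A reader might also infer that the article overstates its power. It does not: Sample size ties the 80% openly to PImax.

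Finally, a statistical analysis plan that is not shown may contain a hierarchy. A general 0.05 statement does not exclude one.

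These points make the percentages conditional and lower the severity. They do not remove the gap. The article itself fixes several primary variables, two metrics and one level for every test. Even the most lenient count of two variables gives 8-10% under any-one-suffices, and the all-must-succeed reading moves the problem to power. Any hidden hierarchy would have to qualify the sentence in Statistical analysis.

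**Conclusion.** The point holds as a should-fix matter. As written, the testing rule does not secure a 5% error across the primary outcomes, because it does not say which result supports the hypothesis.

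The size depends on the reading. Under any-one-suffices with no true effect anywhere, it is about 8-10%, 11-14% or 13-19% for two, three or four variables at assumed correlations of 0.7 to 0, and lower at higher correlations. Under all-must-succeed there is no inflation, but joint power is generally below the PImax figure. Under either reading the swallowing conclusion is not covered by the power calculation. The sample size itself is correct for PImax.

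**What to change.** Before unblinding, add a short statement to the analysis plan that:

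1. names absolute change in cmH2O at the end of training (T1) as the strength metric;
2. names one VFSS scale as the measure of dysphagia severity;
3. controls the primary family with a stated rule. A fixed sequence starting with PImax suits the trial, since PImax is the variable it was sized on and would keep the full 0.05. The order after PImax is partly a matter of preference;
4. labels the other VFSS scale, percentage change and the T2 results as supportive;
5. presents the swallowing result as not covered by the power calculation.

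The cost is a few sentences and no patients, which matters because enrolment closed at 48 (Trial status). The downside of a fixed sequence is that a swallowing result cannot be claimed as confirmatory if an earlier test fails. Holm is an acceptable alternative that keeps that route open; its price is that PImax power could fall to about 63% with three variables, if PImax has to pass at 0.05/3.

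If the data are already unblinded, an order chosen now would not be credible. The report should then present all primary variables together and say that no multiplicity rule was pre-specified.
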